#### Sample Size

We calculated the required sample size for a 2 (between subjects; treatment condition) by 3 (within subjects; time) mixed design, roughly estimating the statistical power needed for the planned linear mixed model for the primary outcome under the assumption of compound symmetry. We used parameters of *f*=0.2 (small to medium effect), =0.05, and power=0.95, resulting in a suggested sample size of 66 to achieve necessary power. We estimate 60% retention throughout the study (40% attrition) based on our initial research [53]; as such, an initial sample of 110 will be recruited.

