### Objectives

The objectives of the study are in response to the goals and needs identified by the community partner, Dilico. Specifically, the primary objective is to determine the effectiveness of the JoyPop app compared to usual practice (UP) in improving emotion regulation among Indigenous transitional-aged youth (aged 18-25 years) who are awaiting mental health services. We hypothesize that youth receiving the app will show improvement in emotion regulation (small to medium effect) greater than that observed for youth receiving only UP.

The secondary objectives are to (1) compare change in mental health difficulties and treatment readiness between youth in each condition to better understand the app’s broader impact as a waitlist tool and (2) conduct an economic analysis to determine whether using the app while waiting for mental health services reduces other health service use and associated costs.

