#### Primary Outcome

We will calculate the change in overall emotion regulation using the DERS-SF total score and the change in specific domains via the DERS-SF subscale scores. An independent statistician will use linear mixed modeling to test whether the change in emotion regulation is greater for those in the intervention condition relative to those in the control condition by including an interaction term between time and group [61]. We will evaluate the final sample to determine whether it is also feasible to analyze gender and baseline mental health symptoms as subgroup effects via interaction terms [62,63]. Analyses will be conducted with an intent-to-treat approach. Missing data will be handled with full information maximum likelihood estimation, which is recommended for avoiding bias in parameter estimates [64,65].

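### The sample size of 66 is arithmetically right, but f=0.2 in the group-by-time interaction is a difference in DERS-SF change of about 0.85 to 0.98 SD, not a small-to-medium effect

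*Protocol article*

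**What the plan says.** The Sample Size section plans for a "2 (between subjects; treatment condition) by 3 (within subjects; time) mixed design", "under the assumption of compound symmetry". Its inputs are given as "0.2 (small to medium effect), =0.05, and power=0.95" (the symbol for alpha was lost in text extraction). The result is stated as "power=0.95, resulting in a suggested sample size of 66 to achieve necessary power", and this is raised to 110 for 40% attrition.

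The Objectives section uses the same words for the primary hypothesis: "youth receiving the app will show improvement in emotion regulation (small to medium effect) greater than that observed for youth receiving only UP". The Primary Outcome section under Statistical Analyses tests this "by including an interaction term between time and group".

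The article gives no correlation between visits and no SD for the DERS-SF. It does not translate f=0.2 into a difference in DERS-SF change.

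**The concern.** The hypothesis and the sample size share one label, so a reader will take it that the trial has 95% power for a small-to-medium advantage of the app over usual practice. The usual benchmarks for f (0.10 small, 0.25 medium) do put 0.2 between small and medium. They match the familiar benchmarks for a standardised mean difference, through d = 2f, only in a simple two-group comparison. The test here is a group-by-time interaction over three visits, where f relates to the group difference in change by a different and much larger factor. If the label is wrong for this test, the article claims high power for an effect that the design may well miss.

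**Working it through.** **Inputs.** From Sample Size: f=0.2, alpha 0.05, power 0.95, two groups, three visits, compound symmetry. From Overview of Study Design: 1:1 allocation. Assumed: a correlation between visits (rho) of 0.5.

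**1. Reproduce 66 and 110.** For the within-between interaction with k=2 groups and m=3 visits:

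- lambda = N × f² × m / (1 − rho) = 66 × 0.04 × 3 / 0.5 = 15.84
- df1 = (k − 1)(m − 1) = 2; df2 = (N − k)(m − 1) = 64 × 2 = 128
- The noncentral F gives power 0.950; N=64 gives 0.944.
- Attrition: 66 / 0.6 = 110.

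Other readings do not give 66. With f=0.2 and 95% power, rho=0.3 needs 92 and rho=0.7 needs 42. A between-group main effect needs 220. Defining f with the correlation already absorbed needs 132 to 198, depending on the convention. So the planning calculation was almost certainly this interaction test at rho=0.5, with f scaled to the single-visit SD.

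**2. Convert f to a group difference in change.** Let the group difference at visit t be δt, in single-visit SDs. The interaction effects are ±(δt − mean δ)/2, and f² is their mean square.

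- Linear divergence (0, D/2, D): effects −D/4, 0, D/4, so f² = (2 × D²/16)/3 = D²/24. At f=0.2, D = 0.2 × √24 = 0.98.
- Full effect at 2 weeks (0, D, D): effects −D/3, D/6, D/6, so f² = (D²/9 + 2 × D²/36)/3 = D²/18. At f=0.2, D = 0.2 × √18 = 0.85. An effect only at 4 weeks (0, 0, D) gives the same.

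This conversion does not involve rho.

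**3. Cross-check.** At rho=0.5 the SD of change is √(2 × 0.5) = 1 single-visit SD. With 33 per arm and D=0.98 (D² = 24 × 0.04 = 0.96), the squared standardised difference is 0.96/(2/33) = 15.84, the lambda of step 1. Simulation with 33 per arm (20,000 runs per scenario) gave power 0.950 for the linear pattern at 0.98 SD and 0.952 for the step pattern at 0.85 SD.

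**4. Power for a small-to-medium difference, read as D=0.4 to 0.5 (an assumption).** 66 completers, 2-df test; in each cell the linear pattern comes first and the step pattern second.

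| rho | power, D=0.4 | power, D=0.5 | D for 80% power | D for 95% power |
|---|---|---|---|---|
| 0.3 | 21%, 27% | 31%, 40% | 0.92, 0.79 | 1.16, 1.00 |
| 0.5 | 28%, 36% | 42%, 54% | 0.77, 0.67 | 0.98, 0.85 |
| 0.7 | 44%, 56% | 64%, 77% | 0.60, 0.52 | 0.76, 0.66 |
| 0.8 | 62%, 75% | 82%, 92% | 0.49, 0.42 | 0.62, 0.54 |

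If all 110 gave complete data, power at rho=0.5 would be 45% to 57% at D=0.4 and 64% to 77% at D=0.5.

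**The case against.** Several points on the other side stand.

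- **The arithmetic is correct.** 66, 110 and 0.95 at f=0.2 all reproduce. A reader might infer that the sample size was miscalculated; it was not. Only the label on the effect is at fault.
- **The article never states a standardised mean difference.** It names f=0.2, and the Objectives use the label without a metric. Reading the label as 0.4 to 0.5 SD is reasonable for a difference in improvement between two groups, but it is the reader's inference.
- **The correlation is unknown.** Reproducing 66 identifies 0.5 as the likely planning value, not as the true one. At 0.7 or 0.8 the detectable differences fall to 0.54 to 0.76 SD at 95% power, which is no longer large. A reader might quote 28% to 36% as the true power; the documents do not support any single figure.
- **66 completers is a floor.** The analysis is by intention to treat with full information maximum likelihood, so partial data from the 110 contribute. The article also does not fix a 2-df test: with time as linear (1 df), D=0.4 with linear divergence has about 36% power at rho=0.5, against 28%.
- **The section calls its own calculation rough**, and an article may leave the correlation to a fuller document.

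A reader might also infer that a null result would be taken as evidence against the app. The article does not say so; it describes only what would follow from positive findings.

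None of this rescues the label. The conversion in step 2 follows from the definition of f and does not depend on the correlation. No correlation from 0.3 to 0.8 brings 66 completers to 95% power at 0.4 or 0.5 SD. Rough planning does not cover a label that describes less than half of the difference powered at D=0.4 (0.4 against 0.85 to 0.98).

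**Conclusion.** The concern holds as a wrong effect-size label, not as a wrong sample size. On the inputs that reproduce 66, the trial has 95% power for a between-group difference in DERS-SF change of 0.85 to 0.98 SD. It does not have that power for the small-to-medium advantage over usual practice in the Objectives. If that advantage means 0.4 to 0.5 SD, power with 66 completers runs from 21% to 92% over correlations of 0.3 to 0.8, and from 28% to 54% at the implied 0.5. These figures assume compound symmetry, a 2-df test and completers only. Because the design, test and recruitment target can stay as they are, this is a correction worth making but not an essential one.

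**What to change.** Keep the sample size. In Sample Size:

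1. State the correlation between visits that was used.
2. Replace the small-to-medium label with the detectable difference in DERS-SF change for 66 completers: 0.85 to 0.98 SD at 95% power and 0.67 to 0.77 SD at 80% power if the correlation is 0.5; 0.66 to 0.76 SD and 0.52 to 0.60 SD if it is 0.7.
3. Give power for a small-to-medium difference, with that difference defined, as a range over plausible correlations rather than as one figure.

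A sentence in Objectives that a non-significant result would not exclude a small-to-medium benefit is optional.

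The cost is wording only, with no added participants. The drawback for the sponsor is that the stated power, or the effect it refers to, becomes less favourable. The Results section reports two participants with all assessments completed by July 2024, so the correction can be made well before any analysis.

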### Ethical Considerations

#### Ethics Approval

The study protocol (version 1) was approved on December 16, 2022, by the Research Ethics Board at the Thunder Bay Regional Health Sciences Centre (file #100157). This Research Ethics Board acts as the Board of Record for clinical research projects led by Lakehead University researchers. The Research Advisory Committee at Dilico reviewed and approved all procedures. All participants will provide informed consent and will be made aware that they will receive counseling regardless of their choice to participate. Any required amendments would be reviewed by the Research Ethics Board, and participants would be informed by phone or email if such amendments directly impacted their experience in the study. We would also update the ClinicalTrials.gov registry (NCT05991154).

#### Mitigation of Harms

The risk of harm due to study participation is minimal. Participants may withdraw at any time by contacting the research team via phone or email. Any concerns or adverse events experienced or reported by participants to a research assistant would be reported immediately to the principal investigator (author [name]). The research team also meets weekly and will discuss any issues or concerns as they arise. All serious adverse events will be reported to the Thunder Bay Regional Health Sciences Centre Research Ethics Board using the Research Ethics Local Serious Adverse Event Reporting Form.

As described earlier, we will provide participants with contact information for local support services during the orientation, including walk-in counseling services and a local crisis line. Additionally, if recent suicidal thoughts are endorsed, an onsite counsellor will conduct a risk assessment with the participant and intervene as needed. As part of this risk assessment, the participant and counsellor will discuss whether continued study participation is recommended. Finally, as participants are on the waitlist for mental health services, they will be offered counseling services at some point following study completion (exact timing based on waitlist at the time).

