**Methods:**

The study is a pragmatic, parallel-arm randomized controlled superiority trial design spanning a 4-week period. All participants will receive UP, which involves waitlist monitoring practices at the study site, which includes regular check-in phone calls to obtain any updates regarding functioning. Participants will be allocated to the intervention (JoyPop+UP) or control (UP) condition in a 1:1 ratio using stratified block randomization. Participants will complete self-report measures of emotion regulation (primary outcome), mental health, treatment readiness, and service use during 3 assessments (baseline, second [after 2 weeks], and third [after 4 weeks]). Descriptive statistics pertaining to baseline variables and app usage will be reported. Linear mixed modeling will be used to analyze change in outcomes over time as a function of condition assignment, while a cost-consequence analysis will be used to evaluate the association between app use and service use.

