## Introduction

### Background

Transitional-aged youth refer to individuals aged roughly 15-26 years who are transitioning from childhood to adulthood, a time of developing independence and increased challenges [1]. In Canada, mental health difficulties among transitional-aged youth have increased across the past decade and during the COVID-19 pandemic [2,3]. Indigenous individuals within this age range experience a greater burden of mental health difficulties compared to their non-Indigenous peers [4,5], partly attributed to distal factors such as a family history of residential school attendance [6] and more proximal factors such as experiences of childhood adversity [7]. Stressors such as substance use, loss of culture, racism, socioeconomic status, and family instability also impact the well-being and mental health of Indigenous youth [8].

Mental health services are less accessible for youth living in remote and rural locations [9]. For instance, there is less use of outpatient-based mental health care and psychiatry services and higher rates of emergency department visits and hospital admissions for mental health-related reasons in Northern Ontario, a region of many different Indigenous communities [10]. In general, long wait times in Northern Ontario are similar to those experienced in other regions of the province [10]; however, wait times for counseling and therapy are particularly long in Thunder Bay compared to many other communities, with an average of 348 days [11]. Services that consider and incorporate culture are even more sparse. Long wait times for services not only delay care and contribute to prolonged distress and suffering but also affect interest and engagement in services once they are offered [12,13].

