### Setting and Participants

Data collection will take place at Dilico Anishinabek Family Care, an Indigenous-led organization that provides culturally informed child welfare, mental health and addictions, and health services to Anishinabek children and adults. Programs and services are provided at individual, family, and community levels. This self-governed organization is situated in Fort William First Nation in Northern Ontario.

Youth will be informed about the study by waitlist case managers and with flyers and letters mailed and emailed to them. Youth will be eligible for trial participation if they are on the waitlist for mental health services at Dilico and between the ages of 18-25 years.

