Service usage will be assessed with 5 items generated by the research team that ask respondents how many times they accessed various health care services (ie, walk-in clinic, family doctor or nurse practitioner, emergency department, mental health counselor, and mental health hotline or phone support) over the previous 2 weeks.

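### The economic objective concerns other services used while waiting, but the single counsellor item cannot separate the awaited Dilico service from other counselling

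*Protocol article*

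**What the plan says.** The second secondary objective (Protocol article, Objectives) is to "determine whether using the app while waiting for mental health services reduces other health service use and associated costs". The abstract's objective likewise refers to other services.

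Secondary Outcome Measures lists five items, each a count over the previous 2 weeks: "walk-in clinic, family doctor or nurse practitioner, emergency department, mental health counselor, and mental health hotline or phone support". Under Statistical Analyses, Secondary Outcomes, the services used in each condition are costed and compared in a cost-consequence analysis. No service is stated to be set apart.

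Four passages bear on whether the awaited service can start during follow-up:

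- Setting and Participants makes youth "eligible for trial participation if they are on the waitlist for mental health services at Dilico" and aged 18-25. No minimum remaining wait is stated.
- The abstract describes a "superiority trial design spanning a 4-week period".
- Mitigation of Harms says that "they will be offered counseling services at some point following study completion (exact timing based on waitlist at the time".
- Ethics Approval says that "they will receive counseling regardless of their choice to participate", without giving a time.

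**The concern.** The objective separates two kinds of contact: the service the youth is waiting for, and services used in the meantime. The outcome list does not. A youth who starts the awaited counselling in week 2 and a youth who sees some other counsellor because of the wait would tick the same item and be costed alike. These mean different things to an agency judging a waitlist tool. The first is the end of the wait; the second is the use that the objective hopes to reduce.

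Once the answers are collected, analysts cannot recover the split from the item. At stake is whether the cost-consequence analysis answers its own question, and whether its incremental cost can be read as the cost or saving in other services.

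**Working it through.** **Can an in-trial visit reach the cost analysis?** Follow-up assessments are at 2 and 4 weeks, and each service item looks back 2 weeks. The two windows therefore cover all 28 days. A visit to the awaited service in that time fits the counsellor item as listed, and the costing rule as stated includes it.

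**Can such a visit occur?** Entry sets no minimum remaining wait. The Mitigation of Harms sentence has two parts: after study completion, and on a date that depends on the waitlist. Both are certain to hold only if no participant reaches the top of the list within 4 weeks, and the stated criteria do not ensure that. No passage says that anyone starts in-trial, and none says that an offer is held back.

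**The plan's own figures, as denominators.** Sample Size gives 66 evaluable and 60% retention: 66/0.60 = 110 recruited, which reproduces. The 66 also reproduces. For the 2 x 3 interaction F test with f = 0.2 and α = 0.05, assuming a within-person correlation of 0.5 (the article gives none), λ = f²·N·m/(1 − ρ) = 0.04 × 66 × 3/0.5 = 15.84 on 2 and 128 df, and power is 0.950.

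**How many could be affected?** The article gives no waiting time for Dilico. Background gives a Thunder Bay figure: "wait times for counseling and therapy are particularly long in Thunder Bay compared to many other communities, with an average of 348 days". Let W be the mean wait. If everyone waits W days and enrols at a random point, the share reaching service in 28 days is 28/W. If exits occur at a constant rate, it is 1 − exp(−28/W). Only W = 348 comes from the document; the other values are assumptions that show the range.

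| W (days) | 1 − exp(−28/W) | 28/W | Of 110 | Of 66 |
|---|---|---|---|---|
| 500 | 5.4% | 5.6% | 6.0-6.2 | 3.6-3.7 |
| 348 | 7.7% | 8.0% | 8.5-8.9 | 5.1-5.3 |
| 180 | 14.4% | 15.6% | 15.8-17.1 | 9.5-10.3 |
| 90 | 26.7% | 31.1% | 29.4-34.2 | 17.6-20.5 |
| 60 | 37.3% | 46.7% | 41.0-51.3 | 24.6-30.8 |

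At 348 days that is about 9 of 110 recruited, or about 5 of 66 evaluable (2 or 3 per arm).

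**Noise or bias?** Let p be the share offered a place within 28 days. Randomisation makes p equal in the two arms in expectation. Let a₁ and a₀ be the acceptance rates among those offered with and without the app, v the mean visits per accepter and c the cost per visit. The awaited service then adds p·(a₁ − a₀)·v·c per participant to the expected cost difference. If a₁ = a₀ this is zero, and only extra variance remains. If a₁ > a₀ it counts against the app, up to 0.08·v·c at p = 0.08. The article gives none of a₁, a₀, v or c.

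**Bound on the primary outcome.** Suppose, as an assumed worst case, that the app had no effect in the 8% who start. Then f falls to 0.2 × 0.92 = 0.184, and power at 66 falls from 0.950 to about 0.91.

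**The case against.** The strongest reply has four parts.

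1. The Mitigation of Harms sentence reads naturally as consistent: counselling comes after the study, on a date the waitlist decides. This stands in part. A reader might infer that the article states that participants enter counselling during follow-up, or contradicts itself outright. It does neither; it leaves an in-trial start possible and unaddressed.

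2. The exact item wording, and the handling of youth who leave the waitlist, may be in the full protocol, which an article condenses. This also stands as a limit. However, the mismatch between an objective about other services and an undivided counsellor item is in the text shown.

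3. Allocation is 1:1 (Randomization and Blinding) and analysis is by intent-to-treat (Primary Outcome), so exits should balance. This is right for who reaches the top of the list. It does not cover acceptance after allocation. The Introduction suggests that the app may reduce disengagement, and treatment readiness is an outcome. That makes a difference in acceptance plausible, but readiness is a 4-item attitude score rather than uptake, and nothing in the article quantifies the route.

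4. Counsellor visits are already a separate item, so they can be reported apart from walk-in, emergency and hotline use. That is true and useful, but it still does not separate the awaited counsellor from any other.

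**Conclusion.** The point holds as a definitional gap in a secondary analysis. As listed and costed, the counsellor item cannot tell the awaited service from other service use, and the text does not rule out a start within the 4 weeks. The size is about 8% (about 9 of 110) if the regional 348-day average applied to Dilico, and about 5% to 47% over assumed mean waits of 500 to 60 days. The expected consequence is noise in the cost comparison, with bias only if the app changes acceptance of an offered place.

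Three stronger readings are not supported:

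- **The incremental cost will have the wrong sign.** This needs a difference in acceptance large enough to outweigh any saving elsewhere, and no figure in the article bears on it.
- **The primary outcome is materially contaminated.** The article gives no comparison of counselling with the app, in-trial starts are only possible, and even the assumed worst case at 8% leaves power at about 0.91. The sample-size figures are not affected.
- **Youth near the top of the list must be excluded.** The trial is expressly pragmatic and had two completers by July 2024, so narrowing entry is a debatable trade-off that this point does not require.

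**What to change.** 1. Split the counsellor item in two: the service the participant was waitlisted for, and any other counsellor. Cost only the second as other service use, and show the first separately by arm.
2. Record the date each participant leaves the waitlist, from agency records, and report exits by arm. Do this before study completion, because Data Management and Confidentiality says the list linking IDs to names is then deleted.
3. Keep every participant in the intent-to-treat analysis, whether or not they leave the waitlist.
4. Reconcile Setting and Participants with Mitigation of Harms on a place that opens during the study. Which rule applies is for the site and the investigators.

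The cost is one extra questionnaire item, one extra date per participant and an amendment through the ethics board. The split will not be available for participants already assessed. With two completers reported as of July 2024, most of the data could still have been collected in the new form at that date.
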